### General objectives

We aim to conduct a Phase I trial to demonstrate the feasibility and safety of non-invasive ventilatory support in cerebral malaria (Blantyre coma scale ≤2) and history of seizures to generate preliminary data on seizure control and neurological status in those surviving to 28 and 180 days.

**
*Specific objectives*
**

**(i)** To initially examine whether it is safe, feasible and practical to implement a protocol for the use of NIV with BCV, with or without the use of Hi-Flow AirVO2 technology (to treat hypercarbia (PCO
_2_))
**(ii)** To implement our refined-protocol for BCV use in cerebral malaria in addition to prophylactic ASM (LVT) to reduce the complications of cerebral malaria.
**(iii)** To estimate the occurrence of adverse events using BCV, including episodes of bradypnoea or apnoea; hypoxaemia (oxygen saturations <92%); number of episodes of hypercarbia (pCo2>45mmHg since this will worse brain swelling), and number of aspiration events (given that all children will routinely having nasogastric tubes and regular suction)

**Site:** High dependency ward in Kilifi County Hospital, Kenya.

**Study design**: Phase I trial to generate feasibility, safety and preliminary data on seizure control and survival to 28 days of non-invasive ventilatory support and seizure prophylaxis in cerebral malaria.

**Study Population:** 30 children hospitalised with cerebral malaria

**
*Inclusion criteria*
**

1. Aged 3 months and 12 years (up to 40 kg in weight for paediatric dosing of LVT) admitted to the paediatric ward.2. Current or recent evidence of
*P. falciparum* malaria (slide or rapid diagnostic test (RDT) positive)3. Blantyre Coma Score2 or less that persists even after correction for concurrent hypoglycaemia (defined as glucose <3 mmol)4. History of seizures in this illness5. Guardian or parent willing and able to provide consent

**
*Exclusion criteria*
**

1. Known cerebral palsy or significant neuro-development delay (which will affect endpoint assessment)2. Skin disease or burns preventing use of the BCV3. Respiratory or cardio-respiratory arrest prior to enrolment4. A comorbidity which clinician believes has a significant risk of poor outcome e.g. malignancy, end-stage renal failure, major cardiac condition

### Sample size determination

This is a Phase I trial designed to test the feasibility, tolerability and safety of using non-invasive ventilatory support in cerebral malaria. We plan to initially enrol 10 children with CM and a history of seizures (see inclusion criteria above) as this selects a high-risk group with ~90% risk of further seizures who will all require first line (diazepam) and many will require second-line (phenobarbitone) anticonvulsants, all with an inherent risk of respiratory depression or aspiration (15% in the control group of the Malawi trial Trials.gov (Trial reference NCT01982812)).

Following this initial phase the next 10 children will receive a neuroprotective strategy of BCV plus LVT 40 mg/kg loading dose and 30mg/kg every 12 hours given via nasogastric tube for 3 days or until coma resolution.

If this reduces seizures that are short lived and are not clinically-relevant (so 80% do not require additional ASM (based on the judgement of an independent Data Monitoring Committee, i.e. that do not require addition ASMs with minimal adverse events), then an additional 10 children will be studied using LVT at this dosage, without dose escalation.

If this fails to adequately control seizures, the neuroprotective strategy of BCV plus a higher dose (150%) of LVT will be studied, namely 60 mg/kg loading dose and 45mg/kg every 12 hours given via nasogastric tube for 3 days or until coma resolution.

## Study procedures

All children admitted with suspected malaria and impaired consciousness (BCS <2) will be screened for study inclusion by the paediatric triage/admission team. Prospective written, informed consent will be sought from parents or guardians of children who are considered to be sufficiently stable. Parents or guardians will be given an information sheet in their usual language containing details of the BCV/LVT study. These will be translated into to local languages, and then back translated (to ensure details are correct) prior to piloting before the initiation of the trial. The sheet will be read aloud to those who are unable to read. Parents and guardians will be encouraged to ask questions about the trial prior to signing the consent form. Consent will include permission for the collection of clinical data and for aetiological investigations. The rights of the participant to refuse to participate without giving reasons must be respected. A number of children will present as emergencies where delay in study enrolment, and thus treatment, will not be practical or indeed humane. We will use a modified form of deferred consent that we developed, received ethical approval for, and used in the FEAST trial. It proposes to use a ‘two-stage’ consent process in this circumstance
^
41
^. Verbal assent will be sought from parents or guardians by the admitting medical team, if it is considered that the full consent process would significantly delay enrolment, and consequently could be detrimental to the child’s health. Full consent will be sought once the child’s clinical condition has been stabilized. Caregivers will be provided with a brief verbal description of the trial and will be given the opportunity to “opt out” of clinical research. The clinician will later sign the verbal assent form, which will be filed with the consent form. If consent is withdrawn later no data from the subject will be used. A social science study of the consent processes used in FEAST found this to be acceptable to parents and health-care workers
^
42
^. As in the FEAST trial, if following an assent process a child died prior to full written consent, full consent would not be sought. This was process of emergency consent was approved (by multiple ethics research committees) for FEAST and has been subsequently approved for use in a transfusion trial in Uganda and Blantyre (TRACT)
^
43
^.

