### Interim reviews

The Data Monitoring Committee (DMC) will review data from the first 10 children enrolled to receive LVT. If the DMC consider that it reduces seizures that are short lived and not clinically-relevant i.e. that 80% do not require addition ASMs then an additional 10 children will be studied using LVT at this dosage. If it fails to adequately control seizures, the neuroprotective strategy of BCV plus LVT for those in coma a higher dose (150%) will be studied, namely a 60 mg/kg loading dose followed by 45mg/kg every 12 hours given via nasogastric tube for 3 days or until coma resolution. In addition to assessing whether or not the 150% higher LVT dose should be tested, the DMC will also review the accumulating safety data after each adverse event potentially related to the intervention (as defined below) occurs, using a Bayesian continuous monitoring approach for safety. The Bayesian approach uses information from other studies to define a prior distribution for an expected rate of an adverse event before the trial starts, thus formally inferring available knowledge on safety on children with cerebral malaria in these settings. After each child completes 72 hours from enrolment, they will be defined as having had a clinically important adverse event potentially related to the intervention or not. This information is used to iteratively update the prior distribution and to estimate a posterior distribution. The posterior distribution is then used to estimate the probability of the clinically important adverse event rate being higher than a defined threshold and is continually updated throughout the trial. If the probability reaches a specific pre-defined value, then the DMC is prompted to consider stopping the trial. Thus, the decision rule to be used by the DMC to consider stopping the trial is based on a high posterior probability (τ) that the estimated percentage of children with clinically important adverse events is above a threshold R (equivalently: Pr(P
_events_>R | data)>τ). Thus, this way of monitoring uses both available knowledge from previous studies and accruing data from the ongoing trial to inform decisions.

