### Trial withdrawal

In consenting to the trial, patients are consenting to trial treatment (BCV with or without prophylactic anti-convulsants), data collection and follow-up. If a carer wishes to withdraw their child from trial treatment, the investigator will explain the importance and benefits of follow-up, and the value of allowing routine clinical data to be used for trial purposes. Patients/parents are free to discontinue any part of their trial treatment or discontinue from follow up. After the participant has entered the trial the clinician remains free to give alternative treatment to that specified in the protocol at any stage if he/she feels it is in the participant’s best interest, but the reasons for doing so should be recorded. In these cases, the participants remain within the study for the purposes of follow-up and data analysis. All carers and participants are free to withdraw at any time from the protocol treatment without giving reasons and without prejudicing further treatment. If they do not wish to remain on trial follow-up, however, their decision must be respected and the patient will be withdrawn from the trial completely.

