### Protocol treatment discontinuation

An individual patient may stop treatment early or be stopped early for any of the following reasons:

▪   Unacceptable toxicity or adverse event

▪   Intercurrent illness that prevents further treatment

▪   Any change in the patient’s condition that justifies the discontinuation of treatment in the clinician’s opinion

▪   Withdrawal of consent for treatment by the patient or parent.

Participation in the trial is entirely voluntary, and parents, carers or older children may choose to discontinue the trial treatment at any time without penalty or loss of benefits to which they are otherwise entitled. Although not required to give a reason for discontinuing their trial treatment, a reasonable effort should be made to establish this reason while fully respecting the patient's rights.

Patients should remain in the trial for the purpose of follow-up wherever possible (unless the patient withdraws their consent for follow-up). If a patient withdraws from the trial, the medical data collected during their previous consented participation in the trial will be kept and used in analysis. This will also apply to parents/carers who withdraw from the trial after assent, that have not completed the deferred consent process. Consent for future use of stored samples already collected can be refused when leaving the trial early (but this should be discouraged and should follow a discussion). If consent for future use of stored samples already collected is refused, then all such samples will be destroyed following the policies of the institution.

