### Statistical analysis

Clinical data will be summarised using means and medians were appropriate for continuous data depending on the distribution. Analyses will follow intention-to-treat. Primary and secondary endpoints will be described using means or medians or proportions. For the primary endpoint (cumulative time with epileptogenic seizure activity over 36 hours), children who die without recovering from coma will be imputed to have a cumulative time of 36 hours (maximum expected coma duration). As this is a Phase I trial no subgroup analyses are planned.

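### Two sections give opposite rules for the data of children enrolled on verbal assent whose parents later withdraw, so the safety and analysis denominators are undefined

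*Protocol article*

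**What the plan says.** Study procedures describes a two-stage process for emergencies: verbal assent at admission, then written consent. On timing it says "Full consent will be sought once the child’s clinical condition has been stabilized". On withdrawal it says "If consent is withdrawn later no data from the subject will be used". On early death it says that "if following an assent process a child died prior to full written consent, full consent would not be sought".

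Protocol treatment discontinuation says that, if a patient withdraws, "the medical data collected during their previous consented participation in the trial will be kept and used in analysis". It then adds: "This will also apply to parents/carers who withdraw from the trial after assent, that have not completed the deferred consent process".

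Trial withdrawal says that if a family declines further follow-up, "the patient will be withdrawn from the trial completely". It does not say what happens to data already collected.

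Two parts of the plan depend on who is counted. Statistical analysis says "Analyses will follow intention-to-treat". Interim reviews feeds a Bayesian safety rule child by child: "After each child completes 72 hours from enrolment, they will be defined as having had a clinically important adverse event" or not. The same section asks the Data Monitoring Committee (DMC) to judge, from the first 10 children on levetiracetam, whether 80% need no additional anti-seizure medication.

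**The concern.** The plan holds two opposite instructions for the same children. Anyone building the analysis set or the DMC report must choose one, and the choice decides whether a treated child is counted.

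Removal under the no-data rule would not be neutral by design. Written consent is sought after stabilisation, so treatment will usually have begun and a complication may already be known when the parent decides. Children who die after assent and before written consent cannot be removed, because consent is then not sought. Only children who survive to the consent discussion can drop out. With 30 children in three groups of 10, a single child is a visible share of any denominator.

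**Working it through.** **1. Can the two rules be separated by scope?**

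- Suppose the no-data sentence covers deferred consent and the keep-data rule covers ordinary withdrawal. This fails, because the keep-data rule is expressly extended to withdrawal after assent with deferred consent incomplete.
- Suppose the no-data sentence covers only families who completed written consent and then withdrew. This also fails, because that is the group to which the keep-data rule applies in the first place.
- Trial withdrawal is silent on data already held, so it does not decide between them.

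The contradiction therefore stands on any reading.

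**2. Reproduce the plan's prior (Interim reviews).** The inputs are Beta(0.23, 1.32), stated mean 0.15 and stated variance 0.05.

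- Mean = a/(a+b) = 0.23/1.55 = 0.148.
- Variance = ab/[(a+b)²(a+b+1)] = 0.3036/(2.4025 × 2.55) = 0.0496.

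Both round to the stated values.

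**3. Effect of removing a child with an event.** The threshold is 20% and the posterior cut-off is 0.95. With x events in n children, compute Pr(P > 0.20) under Beta(0.23 + x, 1.32 + n − x). Children are taken as counted cumulatively across the trial. The first column is the smallest count that crosses 0.95 at that n.

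| All kept | Posterior | One event child removed | Posterior | Still above 0.95? |
|---|---|---|---|---|
| 5/10 | 0.970 | 4/9 | 0.922 | No |
| 6/12 | 0.982 | 5/11 | 0.954 | Yes |
| 7/15 | 0.983 | 6/14 | 0.960 | Yes |
| 8/20 | 0.970 | 7/19 | 0.938 | No |
| 11/30 | 0.976 | 10/29 | 0.954 | Yes |

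At n = 30, removing two event children (9/28) gives 0.916, which is below the cut-off.

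**4. Chance that the rule ever triggers within 30 children.** This is an exact recursion, checked after each retained child. The withdrawal shares are assumptions, since the protocol gives none.

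| True event rate | All kept | 10% of event children removed | 20% | 30% | 10% removed regardless of events |
|---|---|---|---|---|---|
| 30% | 0.504 | 0.409 | 0.311 | 0.221 | 0.474 |
| 40% | 0.852 | 0.775 | 0.667 | 0.538 | 0.820 |

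The loss is material only if withdrawal is related to events.

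**5. The 80% dose review, read as at least 80% of 10 children.**

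- 8/10 = 80% (met). Remove one child who needed no extra medication: 7/9 = 77.8% (not met).
- 7/10 = 70% (not met). Remove one child who needed extra medication: 7/9 = 77.8% (still not met). Remove two: 7/8 = 87.5% (met).

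A single removal changes this result only when a well-controlled child leaves. If poorly controlled children are the ones who leave, it takes two.

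**The case against.** The strongest reply accepts the contradiction and disputes its consequences. A reader might infer that the no-data rule necessarily biases event rates downwards, makes tolerability look better, and lets one deletion reverse either decision. The documents do not support that reading, for these reasons:

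- **No evidence on who withdraws.** There is no withdrawal rate, no figure for how many children will use deferred consent, and nothing linking withdrawal to complications.
- **Intolerance is not withdrawal of consent.** Stopping the device for intolerance or a complication is a treatment stop. Trial withdrawal keeps children whose treatment the clinician changes in follow-up and analysis, and Protocol treatment discontinuation asks that patients stay in follow-up where possible. The claim about tolerability therefore falls away.
- **Direction is open.** Early deaths after assent stay in while survivors can leave, so mortality could be overstated.
- **Boundary cases only.** One removal undoes a stop at some sample sizes and not at others.
- **The DMC is not a machine.** Sample size determination makes the 80% criterion a matter of DMC judgement. Interim reviews says both that the committee is prompted to consider stopping and that enrolment will be stopped. Serious events are reviewed in real time, so the committee may already have seen an event before a withdrawal.
- **Intention-to-treat.** The groups are sequential and not randomised, and excluding a child for lack of consent concerns permission to use data. It is not analysis by treatment received.

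All of this stands as a limit on the consequences. None of it reconciles the two rules or tells the DMC which denominator to use.

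**Conclusion.** The point holds as a direct contradiction over who is counted. Confidence in that is high, because both rules are stated and they cover the same children.

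The consequence is conditional. If withdrawal follows complications, aspiration or respiratory events are under-counted. For example, at a true event rate of 30% the chance of triggering the rule falls from 0.504 to 0.409 if 10% of event children are removed. If withdrawal is unrelated to events, the same 10% costs little (0.504 to 0.474). A certain downward bias, or a decision that always turns on one child, goes beyond what the protocol shows. One child can matter at 10 or 20 children when the count sits on the boundary.

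The inconsistency should be corrected because the trial is reported as ongoing, the DMC needs a defined denominator, and families need one consistent statement about their child's data.

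**What to change.** Reconcile Study procedures and Protocol treatment discontinuation into one rule that agrees with the ethics approvals and the assent and consent forms.

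- **Where those permit,** the preferable rule is that data collected up to withdrawal are kept and used, including in the DMC safety rule and the 80% dose review. Replace the no-data sentence in Study procedures accordingly.
- **Where they require deletion,** state that as the single rule, correct Protocol treatment discontinuation to match, and report the number of children removed per cohort as a limitation of the safety and dose decisions.

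The cost is a short protocol correction and a check of the forms with the ethics committees. It needs no additional patients and no additional data collection.

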### Trial treatments

We will study 30 children. This will be done sequentially (10 children with usual care + BCV; then 10 children with BCV given 40 mg/kg loading dose of LVT and 30mg/kg every 12 hours; and the final 10 children (with or without BCV) will receive LVT but the dose will depend on whether adequate seizure control (see above) has been achieved in the previous 10 children as follows. Firstly, if seizure control is adequate then an additional 10 children will be studied with BCV plus LVT at the same dosage or secondly, if seizure control is not adequate then LVT at a higher dose will be given 60 mg/kg loading dose and 45mg/kg every 12 hours.

The first 10 children in the study will have the usual care for cerebral malaria with the addition of BCV. This will allow us to assess feasibility and tolerability and to provide initial refinements for its use. The BCV ventilation intervention period
**will be from study enrolment** until when a child can respond to stimuli (Blantyre coma scale 3 or more) sustained over a period of 4 hours.

Feasibility will be judged by the ability of BCV to safely institute negative pressure ventilation, and to support respiration during periods of hypoventilation or apnoea. In addition, we will assess whether children are able to tolerate the use of BCV (judged by children remaining comfortable during transition from coma to a semiconscious state) and whether we are able to clear any secretions by regular suctioning (if this is judged to be a problem). Additional practical considerations will be considered such as whether BCV interferes with monitoring the child and time required by the nursing staff to implement and maintain its use.

This will then be followed by a second phase where we will implement a neuroprotective strategy or treatment bundle: where prophylactic ASM will be used in combination immediately following feasibility studies of use of BCV to provide negative pressure ventilation (NPV) +/- AIRVO2 High Flow (children with BCS≤2). We will use LVT at an initial loading dose of 40 mg/kg followed by 30mg/kg every 12 hours. This will be given via nasogastric tube for 3 days or until coma resolution.

### Sampling strategy

Eligible children will have been admitted to High Dependency Unit in Kilifi County Hospital where children can be closely monitored. Here, once malaria and coma status is verified the parents can be approached for consent and, if they agree to participate, enrolled into the trial. Admission blood will be tested for haemoglobin, lactate, blood urea nitrogen (BUN), glucose, and when possible blood gases (including pC02 and base excess)
^
44
^. In addition, we will test for malaria status, and collect usual admission blood samples (full blood count, clinical chemistry, lactate), blood cultures and store plasma on day 0. Management and outcome data will be collected (clinical parameters and recovery, developmental assessment, number of transfusions, and use of drugs (specifically ASMs, paracetamol and antibiotics, date of discharge or in-hospital death)). Contact and locator data will be recorded so that children can be invited by phone of face-face for followed at day 28, day 90 and day 180. This system has worked very successfully in our transfusion trial (TRACT)
^
43
^ with 98% and 95% 90-day and 180-day retention respectively. No additional blood storage will occur after Day 0.

## Clinical assessment

Vital signs will be obtained from bedside patient monitor (temperature, heart rate, respiratory rate, blood pressure, oxygen saturation; conscious level, PCO
_2_ monitoring). During admission, clinical seizures will be timed and recorded. Further seizures will be treated in a standard way as per local guidelines/protocol. Efficacy will be evaluated by the reduction in the number of clinical seizures; the number of additional ASM required and neurological status following survival. Safety (see endpoints section below) will be monitored using the number of aspiration events; the number of episodes of hypercarbia requiring AIRVO2 use; the number of episodes of hypotension (a potential side effect of LVT).

Children will be reviewed daily until discharge and followed up at day 28, day 90 and day 180 for neurological or neurodevelopmental impairments (see
Table 1). Non-compliance is limited by the intervention being administered by clinical teams during admission with careful stopping rules if a child is not able to tolerate the device or develops a complication including aspiration (secondary safety endpoint). Children lost to follow-up before day 180 will be traced for vital status (permission requested within consent) using locator data and multiple contact phone numbers recorded before discharge.

**Table 1. T1:** Patient assessment.

Assessment Time											
Procedure	Adm	1hr	2h	4hr	8hr	12h	24hr	Bi daily until discharge	Day 28	Day 90	Day 180
Clinical assessment	X	X	X	X	X	X	X	X	X	X	X
Laboratory tests *	X				X		X				
Stored blood **	X										
Neurological exam	X									X	X

* Full blood count, clinical chemistry, lactate, glucose, venous blood gases (including pC02 and base excess), blood culture (admission only) **For quantitative plasma HRP2 assessment

